## Abstract

**Background:**

Numerous studies have demonstrated the effectiveness of mindfulness-based programs (MBPs) among both clinical and nonclinical populations. These data document positive impacts in the workplace, including reducing perceived stress and burnout and increasing well-being. However, the effectiveness for productivity, which is of most interest to managers and administrators, is still unclear. In addition, MBPs in the workplace tend to be modified by reducing the number of the program sessions or delivering content online to improve accessibility. To date, however, the impact of MBPs that feature these modifications on productivity in the workplace has not been investigated.

**Objective:**

The study aims to investigate the effectiveness and cost-effectiveness of online-delivered brief mindfulness-based cognitive therapy (bMBCT) for improving productivity and other work-related outcomes among healthy workers compared to the waitlist control.

**Methods:**

We will conduct a 4-week randomized controlled trial (RCT) with a 6-month follow-up. Employees are included in the study if they (1) are between the ages of 20 and 65 years and (2) work longer than 30 hours weekly. Employees are randomly allocated to either the bMBCT group or the waitlist control group. The primary outcome of the study is the mean difference of productivity measured by the World Health Organization Health and Work Performance Questionnaire (WHO-HPQ) between the groups at 4, 16, and 28 weeks. Secondary outcomes include several clinical outcomes and health economics evaluation.

**Results:**

We started recruiting participants in August 2021, and the intervention began in October 2021. A total of 104 participants have been enrolled in the study as of October 2021. The intervention is scheduled to be completed in December 2023. Data collection will be completed by the end of January 2024.

**Conclusions:**

The novelty of the study is that (1) it will investigate bMBCT’s effectiveness on productivity, which is still unclear, and (2) samples are recruited from 3 companies in different industries. The limitations of the study are that (1) all measures assessed are in self-report format and (2) we lack an active control group. This study has the potential to provide new data on the relationship between MBPs and occupational health and productivity.

**Trial Registration:**

University Hospital Medical Information Network Clinical Trials Registry UMIN000044721; https://tinyurl.com/4e2fh873

**International Registered Report Identifier (IRRID):**

DERR1-10.2196/36012

## Introduction

### Background

Mindfulness-based programs (MBPs) are defined as interventions featuring systematic and sustained training in formal and informal mindfulness meditation practices; this training is recognized as central to both the therapeutic approach and the underpinning theoretical model [1]. Numerous clinical trials have demonstrated the effectiveness of MBPs in clinical populations, including patients with depression [2-4], anxiety [5-11], cancer [12-15], and pain [16-20]. These results have been affirmed by the findings of several meta-analyses [21-25].

However, it should be noted that the effectiveness of MBPs is not restricted to clinical populations. MBPs have been shown to be effective in nonclinical populations as well. Existing evidence indicates that MBPs are efficacious for the improvement of stress, sleep, quality of life, and subjective well-being in healthy individuals [26-38]. This is also applicable in the context of occupational health. In their latest meta-analysis of 23 randomized controlled trials (RCTs), Bartlett et al [39] endorsed the effectiveness of MBPs in the workplace for the improvement of numerous clinical factors, such as perceived stress, psychological distress, depression, anxiety, burnout, well-being, and sleep.

### Rationale for the Study

Regarding productivity, which is of most interest to managers, Bartlett et al [39] concluded that productivity was assessed too inconsistently and infrequently for related results to be included in their meta-analysis; thus, they reported the results narratively. Three previous studies have indicated that absenteeism and presenteeism post-MBP intervention show a positive but nonsignificant tendency [35,40,41]; however, one study indicated no effect in that regard [42,43]. Regarding work engagement, although 1 study showed null results [42,43], another study revealed a significant positive effect of MBPs on work engagement [44]. As the inconsistency of the results of previous studies indicates, the effect of MBPs on productivity in the workplace is still unclear. In addition, certain aspects of MBPs, including the delivery mode (eg, online delivery) and the number of sessions, tend to be modified when applied in the workplace to improve accessibility. These modifications are likely to be applied more frequently because of the effects of the COVID-19 pandemic. However, in 85% of the studies included in the meta-analysis by Bartlett et al [39], the interventions were delivered face-to-face and the average number of sessions offered was not necessarily small (7). Thus, the effectiveness of MBPs delivered online and in a small number of sessions for improved accessibility has not been sufficiently investigated, especially in terms of productivity in the workplace.

Therefore, we developed a brief mindfulness-based cognitive therapy (bMBCT) program, which consists of four 1.5-hour sessions, to evaluate the effectiveness and cost-effectiveness of online bMBCT for the improvement of productivity and other work-related indicators compared to the waitlist control.

### Aim

The aim of this study is to investigate the effectiveness and cost-effectiveness of online bMBCT for the improvement of productivity and other work-related outcomes among healthy workers compared to the waitlist control.

## Methods

### Participants

We started recruiting participants in August 2021. The intervention is ongoing and is scheduled to be completed in December 2023. The study is being conducted at the Keio University Center for Stress Research in Tokyo, Japan. The participants are being recruited from among the employees of 3 companies in different industries: Daiwa Securities Group Inc (security), Kumon Institute of Education Co, Ltd (education), and Nichirei Corporation (processed foods). Participants are eligible for the study if they meet the following criteria: (1) aged between 20 and 65 years, (2) work longer than 30 hours weekly, (3) have no history of sick leaves longer than 1 month due to mental disorders or have recovered for longer than 6 months after a sick leave, (4) have physical illnesses but are judged fit to participate in the research by the investigators, (5) score 8 or less in the absolute presenteeism item of the World Health Organization Health and Work Performance Questionnaire (WHO-HPQ), (6) can participate in the intervention and respond to the questionnaires via the internet, and (7) can provide written informed consent. Eligible participants are excluded if they (1) have previously participated in a mindfulness-based intervention for 8 weeks or longer, (2) are unlikely to participate during the research period (eg, they plan to move/relocate), and (3) are judged by the investigators as unfit to participate in the intervention due to physical conditions and other reasons (eg, unstable internet connection). Candidates who score higher than 8 on the WHO-HPQ absolute presenteeism item are allowed to participate in the intervention but will not be included in the RCT. The obtained data will be included in the multivariable analysis described later.

### Enrollment

Prospective participants, who applied for the study via recruiting announcements delivered at each company, received a link to the web screening from the research cooperator at each company. If they passed the web screening, an announcement of the video group orientation was made. In the online group orientation, the research investigators provided written and oral explanations of the study, which included full descriptions of the purpose, significance, and methods of the study; the risks and benefits of participation; and the requirements for consent. Prospective participants were also offered an opportunity to ask questions. The investigators recorded the method, content, and date of the explanations provided. After the online group orientation, individual video interviews were held and the research investigator evaluated whether the participants met the inclusion criteria. Since obtaining written informed consent via online sessions was not feasible, all included participants provided informed consent verbally. The records were converted into PDF files, saved in an electronic storage medium, and stored in a lockable cabinet at the Stress Research Center.

### Baseline Assessment

The included participants completed the questionnaires administered for the collection of demographic and psychosocial data. The psychological assessment tools to be utilized include the WHO-HPQ, the Five Facet Mindfulness Questionnaire (FFMQ), the 9-item Utrecht Work Engagement Scale (UWES-9), the Satisfaction With Life Scale (SWLS), the Flourishing Scale (FS), the Scale of Positive and Negative Experience (SPANE), the Experiences Questionnaire (EQ), the Perceived Stress Scale (PSS), the Investigating Choice Experiments Capability Measure for Adults (ICECAP-A), Team Psychological Safety (TPS), and the Credibility/Expectancy Questionnaire (CEQ). The details of each scale are presented later in the Instruments section.

### Randomization

Eligible participants were randomly allocated to either the bMBCT or the waitlist control group (in a 1:1 ratio). The participants were assigned a computer-generated random number stratified according to company and the baseline WHO-HPQ absolute presenteeism score. The Project Management Office at the Keio Center of Clinical Research, which is an institution independent from the study group, managed the randomization process. The flow of participant recruitment is shown in Figure 1.

**Figure 1 figure1:**
[figure not shown]
Flowchart of the study. bMBCT consists of four 1.5-hour-long sessions (only session 1 lasts for 2 hours). The follow-up session lasts for 1 hour and consists of a short meditation, experience sharing, and a question-and-answer session. bMBCT: brief version of mindfulness-based cognitive therapy; RCT: randomized controlled trial.

### Blinding

Due to the nature of psychological interventions, both the participants and the therapists were not blinded to randomization statuses. Since all measurements obtained during the study are self-reported, there were no assessors for the evaluation of the statuses of participants.

### Interventions

#### Brief Mindfulness-Based Cognitive Therapy

The included participants were offered a bMBCT program, which is a modified version of the original MBCT developed by Segal et al [45]. The modifications followed Crane et al’s [1] specifications of “warp” (essential ingredients) and “weft” (flexible ingredients) of MBPs. To retain the essential ingredients of MBPs, we included practicing all mindful meditations except mindful movement and walking meditation (provided as homework via a delivery instruction movie). In contrast, considering the difference in the delivery setting (clinical setting vs workplace) and the target population (ie, patients with depression vs healthy individuals), some modifications were made. The first is the structure of the program. With the aim of improving accessibility to the program in the workplace, the duration of each session was shortened (from 2 hours to 1.5 hours), except session 1, and the total number of sessions was reduced (from 8 sessions to 4 sessions). To reflect the difference in the target population, the lecture relevant to depression was deleted, and activity records (ie, pleasant, unpleasant, appreciation events, and nourishing and depriving activities) were introduced to enhance the improvement of participants’ well-being. The specific program contents are listed in Table 1. In the program, participants learned both cognitive approaches and mindfulness practices (eg, raisin exercise, body scan, sitting meditation, exploring difficulty, and 3-step breathing space). The participants were asked to practice meditation daily for approximately 20 minutes by listening to the pre-recorded meditation guide audios and record some activities as homework (theme depends on the session). Monthly follow-up sessions (lasts for 1 hour) will be provided to the participants for 6 months. No regular homework will be assigned during the follow-up period. During the follow-up period, the participants can access the mindfulness website developed by the research team from a smartphone or a personal computer (PC) and easily stream/download the meditation instructions.

In addition, the participants were encouraged to send their mindfulness experiences in daily life to the research team. The research team posted and shared them on the website. The research team also posted relevant articles to support participants in continuing the therapy. Participants were encouraged to meditate depending on their needs. In addition to encouraging individual participants to continue meditation, we encouraged them to develop voluntary groups to regularly meditate together outside the program. The bMBCT sessions and follow-up sessions are delivered live outside working hours via a videoconference platform.

The first, third, and fourth authors lead the sessions. The first author is a qualified mindfulness-based stress reduction teacher at the University of Massachusetts, with 12 years of experience in mindfulness practice. The other 2 authors have been practicing mindfulness for more than 5 years and have administered MBCTs 5 times under the supervision of the first author.

**Table 1 table1:** Themes and contents of the program.

Session	Theme	Content
1	Doing mode and being mode/wondering mind	Meditation: raisin exercise/body scan Exercise: What is mindfulness? Homework: mindfulness in a daily activity/body scan.
2	Sensation continues to change/thoughts are not fact	Meditation: mindful movement/breath and body meditation/3-step breathing space Exercise: scenario exercise (thought and feeling exercise) Homework: body scan or breath and body meditation/mindful movement/pleasant-event calendar/3-step breathing space
3	Thoughts are a phenomenon in the mind/thought-body-behavior-mood are connected	Meditation: sound and thought meditation/3-step breathing space Exercise: nourishing activity Homework: sound and thought meditation/unpleasant-event calendar/nourishing activity/3-step breathing space
4	Exploring difficulty	Meditation: exploring difficulty/3-step breathing space Exercise: reflection of the course (“Why am I here?” exercise) Homework: no regular homework (encouraged to practice depending on their need)

### Control Group

Participants in the control group will wait until the intervention group has completed the intervention. During this waiting period, they have been requested not to attend other mindfulness or meditation activities. After the waiting period is completed (ie, 7 months after allocation), the participants in the control group will be offered the same bMBCT but without monthly follow-up sessions.

### Outcomes

#### Primary Outcome

The primary outcome of this study is the mean difference in absolute presenteeism (measured using the WHO-HPQ) between the intervention and the waitlist control (ie, before bMBCT offered) groups at 4 weeks, 3 months, and 6 months postintervention.

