### Sample Size

The primary outcome will be analyzed using the mixed model repeated measurement (MMRM) method to compare the amount of change between groups before and after the intervention (α .05, β .10). To the best of our knowledge, no previous studies have indicated the effect size of MBPs on presenteeism among employees. The sample size was calculated based on the results of a study that showed the effect of MBPs on the quality of life (effect size=0.44) [37]. We estimated that a total of 166 participants are required; however, the sample size was set at a maximum of 220 participants, considering the dropout rate (assumed to be 25%). The dropout rate was referred to the study of an online MBP in the workplace by Aikens et al [44], which reported the dropout rate was 23%.

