### Statistical Analysis

Statistical analyses and reporting of this trial will be based on the intention-to-treat approach. Analyses with complete samples will be also performed to verify the robustness of the results.

The full analysis data set will include all randomized subjects who underwent at least 1 procedure of the intervention.

For baseline variables, we will generate summary statistics with proportions and frequencies for categorical variables and means and SDs for continuous data. For primary and secondary outcome analyses, we will analyze the mean changes from baseline using the MMRM method. Analyses conducted using the MMRM method will include the fixed and categorical effects of intervention, time, and the intervention × time interaction. Imputation will not be performed for missing values, because mixed models can deal with missing data through the maximum likelihood. All comparisons are planned, and all *P* values will be 2-sided. The significance level will be set at 5% for all statistical analyses. All analyses will be conducted using Stata version 16 (StataCorp).

We will also conduct a multivariate analysis to verify the predictors and mediators of the primary and secondary outcomes. A detailed analytical plan will be presented separately.

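### The primary outcome has three unranked time points, two-sided 5% applies to every analysis, and no deciding test is named; if any one time point suffices, the false-positive rate is about 8–14%.

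*Protocol article*

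**What the plan says.** - **Primary Outcome:** the mean difference in absolute presenteeism on the WHO-HPQ "between the intervention and the waitlist control (ie, before bMBCT offered) groups at 4 weeks, 3 months, and 6 months postintervention". None of the three is singled out.
- **Abstract, Methods:** the same three occasions counted from the start of the programme, "between the groups at 4, 16, and 28 weeks".
- **Statistical Analysis:** mean changes from baseline are analysed with a mixed model for repeated measures (MMRM) that "will include the fixed and categorical effects of intervention, time, and the intervention × time interaction". On testing, the section says "All comparisons are planned", that all P "values will be 2-sided", and "The significance level will be set at 5% for all statistical analyses". The only analysis it defers to a separate plan is the one on predictors and mediators.
- **Sample Size:** one α (.05), one β (.10) and one effect size (0.44), to "compare the amount of change between groups before and after the intervention". No week is named.

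**The concern.** Three between-group differences share the status of primary outcome, and nothing says which of them, or what combination, decides whether bMBCT improves productivity. Planning comparisons in advance protects against choosing them after seeing the data. It does not control the error rate across them. Applied as written, the 5% rule would let a productivity claim rest on whichever of three tests is significant, while the sample size was set for a single comparison.

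The three differences also do not measure quite the same thing. At week 4 only the four core sessions have been delivered. The intervention arm is then offered monthly live follow-up sessions for six months, so the later differences reflect the core programme plus follow-up. Results that disagree across time points would be open to competing readings, with no rule to settle them.

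**Working it through.** **Inputs from the article.** Three primary time points (Primary Outcome; Abstract). Two-sided 5% for every analysis (Statistical Analysis). Effect size 0.44, α .05, β .10, 166 participants before dropout (Sample Size). 1:1 allocation (Randomization).

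**Inputs assumed.** The success rule (any one significant time point) and the correlation between the three test statistics. The article gives neither, so the correlation is shown over a range.

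**1. The plan's own figure.** Per arm, n = 2(z₁₋α/₂ + z₁₋β)² / d².
- Two-sided 5%, 90% power: 2(1.960 + 1.282)² / 0.44² = 108.6, so 109 per arm and 218 in total (220 with the t-test).
- Two-sided 5%, 80% power: 2(1.960 + 0.842)² / 0.44² = 81.1, so 82 per arm and 164 in total (166 with the t-test).

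The stated 166 thus matches one two-group comparison at two-sided 5% with 80% power. It does not match the stated β of .10, unless an unstated gain is assumed (adjustment for a baseline correlated about 0.5 with the outcome gives 164). That mismatch is a separate matter. What counts here is that the figure fits one test at an undivided 5%.

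**2. False-positive rate if any one of three tests suffices.** For independent tests: 1 − 0.95³ = 1 − 0.857 = 0.143. For correlated tests, the probability that at least one of three standard normal statistics exceeds 1.96 in absolute value (4 million simulated draws per case):

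| Correlation | Equal for all pairs | Decaying with time (first-order autoregressive) |
|---|---|---|
| 0 | 14.3% (exact) | – |
| 0.3 | 13.6% | – |
| 0.5 | 12.5% | 12.9% |
| 0.7 | 10.9% | 11.4% |
| 0.8 | 9.8% | 10.3% |
| 0.9 | 8.3% | – |

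One point in this range has a simple basis. Suppose the four measurements have equal variances and a common correlation ρ, and changes from baseline are compared without a baseline covariate. Two changes then have covariance 1 − ρ and variance 2(1 − ρ) each, in units of the variance. Their correlation is 0.5 whatever ρ is, and the rate is 12.5%.

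**3. Other success rules.** One named contrast, or one global test, keeps the rate at 5%. Requiring all three to be significant keeps it at or below 5%, but power then cannot exceed that of the weakest single contrast, so the planned β would not describe it.

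**4. Cost of a Bonferroni split instead.** At 0.05/3 per time point the rate is 1 − (1 − 0.05/3)³ = 4.9% for independent tests. With 83 per arm, power per time point is Φ(0.44·√(83/2) − 2.394) = Φ(0.44) = 67%, against 81% at an undivided 5% (same normal formula). Keeping 80% power would need 218 participants before dropout, and 90% would need 280.

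**5. Live sessions offered by each assessment.** 4 by week 4; up to 4 + 3 = 7 by three months; up to 4 + 6 = 10 by six months. The later counts are upper limits, since the assessment windows are ±4 weeks and the article does not say whether a month's session comes before that month's questionnaire.

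**The case against.** The strongest reply is that the article describes one model, not three separate tests. A single overall treatment test from that model, or a rule requiring all three differences to be significant, would not inflate the error rate. The article is also a condensed account, and the contrast and any multiplicity procedure are often left to the full protocol or analysis plan. The first part stands to this extent: the inflated rate is conditional on an any-one rule that the article does not state. The second part does not remove the point. The article itself makes three time points primary and sets 5% for all analyses, and it refers only the predictor and mediator work to a separate plan.

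Three stronger readings are tempting, and the document does not support them.

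- **That the error rate simply is 11–14%.** This needs the any-one rule and correlations no higher than about 0.7. Neither is stated, and at 0.8 to 0.9 the rate is about 8–10%.
- **That week 4 is the contrast the trial was powered for.** The Sample Size section speaks only of before and after the intervention. The Control Group section has controls wait until the other arm has finished the intervention and ends that wait seven months after allocation, so the word can also cover the follow-up period.
- **That an effect seen only at six months would miss the trial's question.** The stated aim is online bMBCT against waitlist. The rationale describes four sessions, but the follow-up sessions are described under the bMBCT heading and sit in the bMBCT row of the assessment schedule. The randomised comparison is bMBCT with follow-up against waitlist. A late effect answers that comparison; it cannot be credited to the four core sessions alone.

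**Conclusion.** The point holds in conditional form. The article fixes three unranked primary time points and a blanket two-sided 5%, supplies no deciding test or error control, and sizes the trial for one comparison. If any one significant time point counts as success, the chance of a false claim on the primary outcome is about 8–14%, or 1.7 to 2.9 times the nominal 5%, for correlations from 0.9 down to 0. No correlation is given in the document, so no single figure can be asserted. The absence of a deciding test rests on the text alone; the size of the inflation rests on the assumed success rule and correlation. A separate analysis plan that names one deciding test would settle the matter, provided that it predates any comparison of outcome data.

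**What to change.** Before outcome data are compared, state one deciding test for the primary outcome at two-sided 5%. It should be one of these:

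1. one MMRM contrast at a named time point; or
2. one test over all three visits, either the average treatment effect or a joint test that all three differences are zero.

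If the second is chosen, the intervention × time interaction alone will not serve when the responses are changes from baseline. It asks whether the effect varies between visits and would miss a constant benefit.

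Test the remaining time points in a stated fixed sequence at 5%, or report them as supportive with confidence intervals. The choice of time point belongs to the sponsor. Week 4 is one candidate, because only the four core sessions precede it, though the sample-size text does not name it. Describe the 3- and 6-month contrasts as bMBCT plus monthly follow-up sessions. Align the Sample Size section with the chosen test.

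The cost is wording only, with no extra participants when the deciding test is a single contrast. A global or average test should have its power checked against the planned number. The drawback of a fixed sequence is that a later time point cannot be claimed alone if the first test fails.

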#### Secondary Outcomes

The secondary outcomes are the mean differences in the FFMQ, UWES-9, SWLS, FS, SPANE, EQ, PSS, ICECAP-A, TPS, and SEC scores at 4 weeks, 3 months, and 6 months postintervention.

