### Instruments

#### World Health Organization Health and Work Performance Questionnaire

The WHO-HPQ is a self-report instrument designed to estimate the workplace costs of health problems in terms of self-reported sickness absences and reduced job performance (presenteeism). Presenteeism is assessed using the following questions: “On a scale of 0-10, where 0 is the worst job performance anyone could have at your job and 10 is the performance of a top worker, how would you rate the usual performance of most workers in a job similar to yours?” and “Using the same 0-10 scale, how would you rate your overall job performance on the days you worked during the past 4 weeks?” A low presenteeism score indicates poor performance [46].

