### Schedule for Assessments

In addition to the baseline assessment, we requested that the participants respond to these self-report assessments at 4 weeks, 3 months, and 6 months postintervention. A range of ±2 weeks from the scheduled dates for the baseline and postintervention assessments and ±4 weeks for the 3- and 6-month postintervention assessments were allowed. All assessment data were collected using the electronic patient-reported outcomes (ePRO) system. The assessment schedules are presented in Tables 2 and 3.

**Table 2 table2:** Assessment schedule for all participants.

Process/assessment	Screening period	Intervention period					Follow-up period						
		Week 1	Week 2	Week 3	Week 4	1 month		2 months	3 months	4 months	5 months	6 months	
Screening	A^a^	N/A^b^	N/A	N/A	N/A	N/A		N/A	N/A	N/A	N/A	N/A	
Informed consent	A	N/A	N/A	N/A	N/A	N/A		N/A	N/A	N/A	N/A	N/A	
bMBCT^c^	N/A	I^d^	I	I	I	F^e^		F	F	F	F	F	
Waitlist	N/A	N/A	N/A	N/A	N/A	N/A		N/A	N/A	N/A	N/A	N/A	
WHO-HPQ^f^	A	N/A	N/A	N/A	A	N/A		N/A	A	N/A	N/A	A	
FFMQ^g^	A	N/A	N/A	N/A	A	N/A		N/A	A	N/A	N/A	A	
UWES-9^h^	A	N/A	N/A	N/A	A	N/A		N/A	A	N/A	N/A	A	
SWLS^i^	A	N/A	N/A	N/A	A	N/A		N/A	A	N/A	N/A	A	
FS^j^	A	N/A	N/A	N/A	A	N/A		N/A	A	N/A	N/A	A	
SPANE^k^	A	N/A	N/A	N/A	A	N/A		N/A	A	N/A	N/A	A	
EQ^l^	A	N/A	N/A	N/A	A	N/A		N/A	A	N/A	N/A	A	
PSS^m^	A	N/A	N/A	N/A	A	N/A		N/A	A	N/A	N/A	A	
ICECAP-A^n^	A	N/A	N/A	N/A	A	N/A		N/A	A	N/A	N/A	A	
TPS^o^	A	N/A	N/A	N/A	A	N/A		N/A	A	N/A	N/A	A	
CEQ^p^	A	N/A	N/A	N/A	A	N/A		N/A	A	N/A	N/A	A	
Health service use	A	N/A	N/A	N/A	A	N/A		N/A	A	N/A	N/A	A	
Homework engagement/qualitative data	N/A	A	A	A	A	A		A	A	A	A	A	

^a^A: assessment.

^b^N/A: not applicable.

^c^bMBCT: brief mindfulness-based cognitive therapy.

^d^I: intervention.

^e^F: follow-up.

^f^WHO-HPQ: World Health Organization Health and Work Performance Questionnaire.

^g^FFMQ: Five Facet Mindfulness Questionnaire.

^h^UWES-9: 9-item Utrecht Work Engagement Scale.

^i^SWLS: Satisfaction With Life Scale.

^j^FS: Flourishing Scale.

^k^SPANE: Scale of Positive and Negative Experience.

^l^EQ: Experiences Questionnaire.

^m^PSS: Perceived Stress Scale.

^n^ICECAP-A: Investigating Choice Experiments Capability Measure for Adults.

^o^TPS: Team Psychological Safety.

^p^CEQ: Credibility/Expectancy Questionnaire.

**Table 3 table3:** Assessment schedule for participants in the waitlist control group, followed by a waiting period.

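### The primary outcome wording mixes two time origins, and under the week-4 reading the ±2-week window accepts a first post-programme form at week 2, mid-programme

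*Protocol article*

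**What the plan says.** The article gives the timing of the primary outcome in several places.

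- **Primary Outcome:** the comparison is between the "groups at 4 weeks, 3 months, and 6 months postintervention". Secondary Outcomes uses the same list ("scores at 4 weeks, 3 months, and 6 months postintervention"), and so does the text of Schedule for Assessments ("respond to these self-report assessments at 4 weeks, 3 months, and 6 months postintervention").
- **Abstract, Methods:** the design is a "4-week randomized controlled trial (RCT) with a 6-month follow-up", and productivity is compared "between the groups at 4, 16, and 28 weeks".
- **Table 2** ("Assessment schedule for all participants"): after screening, the WHO-HPQ is marked at Week 4 of the intervention period and at months 3 and 6 of follow-up. The 1-month follow-up column is marked not applicable.
- **Window, Schedule for Assessments:** "A range of ±2 weeks from the scheduled dates for the baseline and postintervention assessments" is allowed, and ±4 weeks for the 3- and 6-month assessments.
- **Instruments, WHO-HPQ:** the presenteeism item asks about "overall job performance on the days you worked during the past 4 weeks".

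**The concern.** There are two linked problems.

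First, the section that defines the primary outcome attaches one qualifier to a list with two time origins. The 3- and 6-month points run from the end of the programme. The 4-week point, if it is to agree with the abstract and Table 2, must run from the start. A reader of that section alone would schedule the first assessment four weeks too late.

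Second, settling the wording as week 4 leaves a fault in the window. Two weeks before week 4 is the middle of the programme. The item looks back four weeks, so a form completed then asks partly about work done before any session. It would still count as a valid form for the first primary contrast, which it pulls towards zero.

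**Working it through.** **Inputs.** Programme length 4 weeks (Abstract, Methods; Table 2). Stated time points 4, 16 and 28 weeks (Abstract, Methods). Windows ±2 weeks and ±4 weeks (Schedule for Assessments). Recall period 4 weeks (Instruments, WHO-HPQ). Convention: 3 months = 12 weeks and 6 months = 24 weeks, counting week 0 as session 1 and week 4 as the end of the programme.

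**Step 1: reproduce the abstract's time points.**

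- First visit at the end of the programme, later visits counted after it: 4 + 0, 4 + 12, 4 + 24 = weeks 4, 16, 28. This matches the abstract and Table 2.
- Qualifier applied to all three points: 4 + 4, 4 + 12, 4 + 24 = weeks 8, 16, 28. This does not match.

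The two readings differ only at the first point.

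**Step 2: what the item covers.** A form completed at week t covers weeks t − 4 to t.

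| Form completed at | Recall period | Weeks before session 1 |
|---|---|---|
| week 4 (nominal) | 0 to 4 | 0 |
| week 3 | −1 to 3 | 1 of 4 |
| week 2 (earliest allowed) | −2 to 2 | 2 of 4 |

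**Step 3: dilution of a single early form.** Assume that the answer averages performance evenly over the recall period, and call the full effect 1.

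- *Immediate full effect at session 1.* The share carried is t/4: week 4 gives 1, week 3 gives 0.75, week 2 gives 0.50.
- *Linear build-up to the full effect at week 4.* The effect at week s is s/4, so the share is (t²/8)/4 = t²/32. Week 4 gives 16/32 = 0.50 and week 2 gives 4/32 = 0.125. A week-2 form then carries 0.125/0.50 = one quarter of what an on-time form carries.

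**Step 4: effect on the first contrast.** Let p be the share of intervention-arm forms completed at week 2, with the rest on time. Relative to all forms on time, the contrast is 1 − 0.5p (immediate effect) or 1 − 0.75p (linear build-up). The article does not give p. Assumed values, for illustration only:

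| p | Immediate | Linear |
|---|---|---|
| 10% | 0.95 | 0.925 |
| 25% | 0.875 | 0.8125 |

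**Step 5: the later visits.** With ±4 weeks, the earliest forms fall at weeks 16 − 4 = 12 and 28 − 4 = 24. Their recall periods are weeks 8 to 12 and 20 to 24, both wholly after the programme.

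**The case against.** The strongest reply is that the article settles the timing itself. The abstract's figures work only with a week-4 visit. Table 2 leaves the 1-month follow-up column, where a week-8 visit would fall, without a WHO-HPQ. The window sentence calls the first visit simply postintervention, apart from the 3- and 6-month ones. The list can also be parsed as 4 weeks, followed by 3 and 6 months after the intervention. This stands: week 4 is the intended time, and the wording is loose rather than a second schedule. It does not answer the window point, which arises precisely under the week-4 reading.

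A second reply is that a ±2-week tolerance is ordinary, openly stated and the same in both arms, so early forms can at most dilute. That is fair as to direction, since dilution is not bias in favour of the programme. But a tolerance equal to half the length of the programme and half the recall period is not neutral for a visit meant to follow the programme.

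A reader might also infer that the waitlist arm has no anchor of its own. The article does not support that: Table 2 covers all participants, and Control Group ties the waiting period to 7 months after allocation.

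**Conclusion.** The point holds as a wording fault in three sections and a badly placed early edge of one window. It should be corrected, but it does not undermine the trial. A form at week 2 loses about half of its effect if the benefit is immediate, and more if it builds gradually. This rests on even averaging over the recall period. The loss over the whole first contrast cannot be given from the article.

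Two stronger readings are not supported:

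- **That the two timings measure wholly separate periods of work.** At nominal dates the recall periods are weeks 0 to 4 and 4 to 8, with no overlap. With ±2 weeks, both visits could be answered at week 6 and the recall periods would then coincide for all 4 weeks. Nor is week 8 a live option once Table 2 is read.
- **That power for the first contrast collapses.** With the planning effect of 0.44 and 83 per arm, a t-test gives about 80% power. Linear build-up would reduce the effect to 0.22 at week 4 (about 29%) and 0.055 at week 2 (about 6%). Those lower figures need an assumed build-up with no basis in the article, a single-time-point test instead of the planned mixed model over three visits, and, for the last, every form at the extreme edge of the window. The gap between week 8 and week 4 would also not be recovered by any correction that keeps week 4.

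**What to change.** 1. In Primary Outcome, Secondary Outcomes and Schedule for Assessments, state one time origin: weeks 4, 16 and 28 from the first bMBCT session, with the same calendar dates for both arms. This adopts the schedule already in the abstract and Table 2.
2. Accept the first post-baseline questionnaire only from session 4 onward, within 0 to +2 weeks of the scheduled week-4 date, with the same calendar window in the waitlist arm. The ePRO system needs an opening date for that form.
3. For cohorts already assessed, report the actual completion dates by arm. Run a sensitivity analysis of the primary outcome that excludes first post-baseline forms completed before session 4, using the matching calendar date in the waitlist arm.

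The cost is a change of wording, one system date and one additional analysis. The downside is a narrower window, and perhaps a few more late or missing forms at the first assessment.
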